**Fig. 1 Fig1:**
[figure not shown]
Flowchart of study participation

Participants in the intervention condition will complete eight weekly training sessions that include a virtual reality active gaming component (i.e., PT component), with CBT strategies that increase balance confidence by addressing subject-specific avoidance behaviors and maladaptive cognitions. Each session will last approximately 1.5 h. Participants in the control condition will complete a series of at-home upper-body seated exercises during this 8-week period after being taught by a physical therapist how to perform the exercises. The intention of the sham control is to blind participants to the study group. At the start of the study and at 8 (post-intervention), 16, and 24 weeks following group allocation, participants will complete survey-based outcome measures and activity monitoring. At baseline and post-intervention, participants will complete performance-based assessments of balance and of functional mobility. Outcomes measures are described below.

To minimize loss to dropout between baseline and final follow-up, research coordinators will routinely contact participants by telephone and email to maintain engagement in order to maximize participant adherence. Adherence will be quantified based on number of study visits attended and frequency of attendance. If a participant wishes to drop out of the study, they will be queried as to their reasons for doing so and every attempt will be made to address their concerns and to obtain the minimum amount of data necessary to address hypotheses related to the primary outcome (i.e., self-reported measures at 0 and 25 weeks).

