### Sham-control condition

Participants assigned to the control condition will be introduced to three exercise modules (Modules A–C) that include seated exercises to improve core and arm strength and flexibility. All of the exercises are demonstrated to the participant by a physical therapist at the initial session. Participants will be provided a manual with thorough descriptions and visual aids of the seated exercises. Some of the exercises include use of a resistive (plastic air-filled) ball, which will also be provided to the participant. Participants will be instructed to start with Module A and continue for weeks 1–3, followed by Module B for weeks 4–6, and to finish with Module C for weeks 6–8. Participants will be told to follow the modules at their own pace. Each module includes approximately eight exercises that take 15–20 min to complete and participants will be told to work on the exercises three days per week. Participants will be provided a worksheet to record exercise days. Participants will be contacted by phone every 2–3 weeks during the 8-week intervention period to maintain engagement and encourage completion of the follow-up assessments.

The control is intended to account for a potential placebo effect and is considered a sham-control in that none of the exercises target lower extremity strength or flexibility, which is more likely to induce functional improvements and promote balance confidence during weight-bearing activities.

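### The control cannot blind participants to the treatment they receive or equalise therapist contact, so a difference in self-rated ABC supports a claim about the whole CBPT package, not about CBPT beyond attention and expectancy

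*Protocol article*

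**What the plan says.** The protocol gives the control two purposes. Under Study design: "The intention of the sham control is to blind participants to the study group". Under Sham-control condition: "The control is intended to account for a potential placebo effect and is considered a sham-control". The reason given there for calling it a sham is that its exercises leave out lower-limb strength and flexibility.

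The arms are described as follows.

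- **CBPT** (Study design): "eight weekly training sessions that include a virtual reality active gaming component (i.e., PT component), with CBT strategies". On length: "Each session will last approximately 1.5 h". A physical therapist and a behavioral therapist deliver the sessions. Session 1 includes teaching on how the games can help balance and how balance confidence affects behavior.
- **Control** (Study design): "Participants in the control condition will complete a series of at-home upper-body seated exercises during this 8-week period". Under Sham-control condition: "All of the exercises are demonstrated to the participant by a physical therapist at the initial session". After that: "Participants will be contacted by phone every 2–3 weeks during the 8-week intervention period". The stated aim of the calls is engagement and completion of follow-up.

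Study design also says that the participant is told the group assignment at a visit about one week after enrollment. The primary outcome, ABC, is the participant's own rating. Blinding is described for the assessor of the Berg Balance Scale (BBS) and L-test and for the person who processes the activity data. Limitations concedes that CBT and PT effects cannot be separated, and it mentions a standard-care comparator for a later study as a matter of clinical feasibility. It does not mention unequal contact, expectancy or participants' knowledge of their treatment.

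**The concern.** A sham supports attribution to content only if the arms are alike in what participants experience apart from that content. Here the control lacks both visible components of CBPT and nearly all of its therapist contact. The rationale taught in session 1 has no described counterpart in the control arm. With a self-rated primary outcome, differences in attention, expectation and willingness to report improvement can enter the group-by-time effect.

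What is at stake is the wording of the main conclusion. As the protocol stands, a positive ABC result could be reported as participant-blinded and placebo-controlled, which its own description of the arms does not support. The Aim 1 outcomes best protected from rating bias, BBS and L-test, offer no check. Analysis plan tests them only before against after by paired t-test and expressly not between groups, although Aim 1 itself is framed as a comparison with sham.

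**Working it through.** **1. The stated purposes against the design**

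| Property | What the protocol describes | Secured? |
|---|---|---|
| Participant unaware of the treatment received | Assignment disclosed; laboratory games plus CBT versus seated exercise at home | No |
| Participant unaware of which arm is the sham | Depends on consent wording, which is not shown | Cannot be judged |
| Equal contact | See step 2 | No |
| Equal rationale and expectancy | Rationale taught in CBPT session 1; none described for controls | Not shown |

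**2. Contact**

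- CBPT, scheduled: 8 sessions × 1.5 h = 12 h.
- Control, in person: one demonstration, length not stated. If it lasts 0.5 to 1.5 h (assumption), the in-person gap is 12 − 1.5 = 10.5 h to 12 − 0.5 = 11.5 h.
- Control calls: 8 ÷ 3 = 2.7 to 8 ÷ 2 = 4, so about 2–4.
- Control exercise, unsupervised: 8 weeks × 3 days × 15–20 min = 6–8 h. This is activity, not contact.

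**3. The protocol's own sensitivity figure**

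Inputs (sample-size paragraph under Participants): N = 60, 2 groups, 4 time points, power 0.80, alpha 0.05, correlation 0.50. For the within-between interaction, λ = f² × N × m ÷ (1 − ρ) = f² × 60 × 4 ÷ 0.5 = 480 f². The degrees of freedom are (2 − 1)(4 − 1) = 3 and (60 − 2)(4 − 1) = 174. Solving for power 0.80 gives f = 0.1524, and power at f = 0.152 is 0.798. The stated f = 0.152 reproduces.

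**4. Illustration: a purely non-specific shift**

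Assume that CBPT content has no effect on ABC and that contact and expectancy raise it by d SD at all three follow-ups. The protocol gives no value for d; the range is assumed.

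- Between-arm differences over the four visits are 0, d, d, d, with mean 0.75d.
- Interaction terms are half the deviations from that mean: ±0.375d once and ±0.125d three times.
- f = d × √[(0.375² + 3 × 0.125²) ÷ 4] = 0.2165d.

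| Assumed shift d | f | λ = 480 f² | Probability that the interaction test is significant |
|---|---|---|---|
| 0.2 SD | 0.043 | 0.90 | 11% |
| 0.3 SD | 0.065 | 2.03 | 19% |
| 0.5 SD | 0.108 | 5.63 | 48% |

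A shift present at week 8 only (0, d, 0, 0) has mean 0.25d and half-deviations of 0.375d once and 0.125d three times, hence the same f and the same probabilities. For the interaction test, then, the illustration does not need the shift to last.

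**The case against.** **The protocol states intentions, not achieved blinding.** This is fair. A reader might infer that blinding has been shown to fail. The documents do not support that: participants who know their programme may still not know which arm is the sham, and the consent wording that would settle this is not shown. What stands is narrower. No consent wording can hide the treatment received or equalise contact.

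**Changed beliefs are the target of CBPT.** When the outcome is confidence, teaching about confidence is part of the treatment and not clearly a placebo element. This stands, and it is one reason why the package comparison is legitimate. It does not make the control one that accounts for placebo.

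**Nothing shows that attention or expectancy moves ABC as much as CBPT would.** Correct. A reader might conclude that non-specific effects explain a positive result equally well; no figure in the protocol supports that. Only the weaker statement holds, that they cannot be excluded.

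**The percentages are not type I error.** Also correct. The test of package versus control keeps its 5% level. The figures show how often an assumed non-specific difference, itself a real difference between the packages, would be significant and could be credited to content.

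**Contact is not 12 h against nothing.** Controls have a therapist session and calls, coordinators contact participants in general, and Discussion allows the number of sessions to be modified. The gap is somewhat under 12 h as scheduled. It remains large.

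**BBS and L-test should not be a gate.** A reader might want to require support from them before accepting an ABC effect. Background argues against that, because balance confidence may be partly independent of function. A true difference of 0.5 SD with 30 per arm would also be detected only about 48% of the time, and these tests are not repeated after week 8. They can support an ABC finding but should not be a condition for it.

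**Conclusion.** The point holds as one about what the control can claim. The protocol assigns it two purposes, participant blinding and accounting for placebo. The design secures neither knowledge-free treatment nor equal contact, and Limitations does not say so. The scheduled contact is 12 h against one demonstration and about 2–4 calls. This follows from the protocol's own description and needs no assumption beyond the length of the demonstration.

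The randomised comparison of the whole CBPT package with low-contact home exercise is sound. A difference in self-rated ABC cannot, however, be attributed to CBPT beyond attention, expectancy and reporting. How much these contribute is unknown. The figures of 11%, 19% and 48% rest on assumed shifts of 0.2, 0.3 and 0.5 SD, 30 per arm, correlation 0.50 and sphericity, and they are illustrative only. The documents do not establish that blinding failed in the sense of participants knowing which arm is the sham, that bias accounts for any particular share of an effect, or that the test's error rate is inflated.

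**What to change.** 1. **Wording.** In Study design and Sham-control condition, replace the blinding and placebo statements with a statement that participants are not blinded to the treatment received and that therapist contact is unequal. Word the conclusion as the CBPT package versus low-contact home exercise, and add the point to Limitations.
2. **Supporting analysis.** In Analysis plan, add a between-arm comparison of the change in BBS and L-test from baseline to week 8. Study design has participants complete these tests at both times without limiting this to one arm, and a blinded assessor scores them. Report the result with the between-arm step counts already planned under Hypothesis 2a, as supporting evidence and not as a condition for an ABC claim.
3. **Optional.** Add an expectancy item after the first post-allocation visit and an arm-guess item at week 8 to the surveys, for participants who have not yet passed those visits.

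Items 1 and 2 need no new data, staff or visits. The price is a more modest claim for the control arm. Data for item 3 will be incomplete because, according to Trial status, recruitment began in April 2018.

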### Setting and ethics approval

The study will be performed at the Human Performance Laboratory at Rosalind Franklin University of Medicine and Science, North Chicago, IL, in conjunction with investigators at the Captain James A. Lovell Federal Health Care Center, North Chicago, IL, Edward Hines Jr. Veterans Administration Hospital, Hines, IL, and Northwestern University, Chicago, IL. The protocol described herein has already received institutional review board (IRB) approval from all study sites. Any modifications to the approved protocol or reporting of adverse events will be submitted to the IRB by the study PI according to published IRB policies.

### Participants

Participants will be veterans recruited directly from local VA Medical Centers or civilians/veterans recruited from the community. Recruitment at local VA hospital centers will take place through a two-step process. In step 1, medical records will be reviewed for persons having a unilateral transtibial amputation and prescribed prosthesis at least 6 months prior. Veterans found through medical record search will be sent a form letter indicating they may qualify for a study and should respond to the letter only if interested in additional information. The letter will ask them to complete and return a copy of the Activities-specific Balance Confidence (ABC) scale. In step 2, participants with ABC scores less than 80% will be called by research coordinators to determine eligibility through the use of an IRB-approved script. Recruitment of civilians/veterans from the community will primarily take place through flyers posted at local prosthetic clinics, support groups, and physical therapy offices.

All participants must meet the following criteria: at least 18 years of age, unilateral transtibial amputation, at least 6 months experience with using a definitive prosthesis, an ABC score less than 80. Participants will be excluded for open wounds on weight-bearing surfaces, inability to stand unassisted and weight-shift for 2.5 min (i.e., inability to perform the CBPT intervention), ill-fitting or ill-functioning prosthesis as determined during a screening with the study prosthetist, prohibited by primary care physician or research physician to engage in mild exercise, history of neurodegenerative diseases and stroke, or currently receiving physical therapy. No other concomitant therapies or interventions are excluded from the study and all other standards of care are permitted. Screening and all other study-related activities will occur only after the participant provides written informed consent, which will be taken by a study team member.

It is expected that 70 participants will be recruited in order to obtain a total of 60 eligible participants (30 intervention and 30 control participants), assuming a 15% drop-out rate. Using G*Power 3.1, a sensitivity analysis (with regard to Hypothesis 1a) was conducted, specifying a power of 0.80, an alpha of 0.05, and an average correlation of observations of 0.50. According to the analysis, with 30 participants in each group we will be able to detect a small to medium effect (f = 0.152) of intervention on ABC score over time with this design, which is consistent with the size of effect observed for older adults [10, 11]. We will have similar power for all hypotheses in Aim 2, which use the same analysis as Hypothesis 1a; we will have power to detect a medium effect size (d = 0.46) for Hypothesis 1b and a correlation of r ≥ 0.42 for Hypothesis 3.

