### Outcome measures

Outcomes will be collected before the start of the intervention (baseline) and again at 8 weeks (post-intervention), 16 weeks, and 24 weeks following group allocation.

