### Analysis plan

To test Hypothesis 1a we plan to use a 2 (group) × 4 (time point) mixed ANOVA to examine if there are significant differences in changes in ABC scores between the groups (i.e., an interaction effect), accounting for any missing data. In the event of a significant interaction, a post-hoc paired *t*-test will be used to compare ABC scale in the intervention group at 0 and 25 weeks and independent samples *t*-test to compare ABC scale between groups at 25 weeks.

To test Hypotheses 1b and 1c we will use a paired *t*-test to compare BBS scores and L-test times pre- and post-intervention. H1b and c do not compare time-related changes in performance between groups as they are only intended to assess the immediate effects of intervention.

The same analyses from Hypothesis 1a will be used to test all hypotheses in Aim 2. For Hypothesis 2a, a group × time interaction on self-reported community participation measures (CRIS, FAI, SF36 scales) and objective measures from the activity monitors will be tested. A false-discovery rate correction method will be used to minimize the likelihood of type I errors. For Hypothesis 2b, an interaction on the QoL score will be tested. In the event that H2a is not supported, alternative measures to assess integration will be considered.

To test Hypothesis 3 changes in ABC scores (0 weeks to 25 weeks) will be correlated with changes in self-reported and objective measures of community participation. A false-discovery rate correction method will be administered to minimize the likelihood of type I errors. In the unlikely event that Hypotheses 1a and 2a are not supported, this would not exclude the possibility of an association between subject-specific changes in confidence and participation. In such a case, a significant correlation would suggest that improving balance confidence can increase participation, but for optimum effectiveness of the intervention, one should only train individuals who are most likely to respond to the intervention (show large increase in ABC scores). As an initial step to identify commonality among “responders” we would employ a suite of supervised learning techniques (e.g., cluster and canonical correlation analysis) to explore multidimensional relationships among responses to individual items on the ABC, BBS, CRIS, and SF36.

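### After a significant interaction, the only follow-up test of ABC change is uncontrolled and within the CBPT arm; because entry is capped on the same scale, that gain should not be read as the effect of CBPT.

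*Protocol article*

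**What the plan says.** Under Participants, eligibility requires "at least 6 months experience with using a definitive prosthesis, an ABC score less than 80". For the VA route, "The letter will ask them to complete and return a copy of the Activities-specific Balance Confidence (ABC) scale", and then "participants with ABC scores less than 80% will be called by research coordinators to determine eligibility". For community recruits the article describes flyers but no separate ABC before the visit, and it places screening after written consent.

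Outcome measures makes ABC the primary outcome and gives the timing: "Outcomes will be collected before the start of the intervention (baseline) and again at 8 weeks (post-intervention), 16 weeks, and 24 weeks following group allocation". It does not say whether the qualifying score may stand as the baseline value.

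Under Analysis plan, Hypothesis 1a is tested by a "2 (group) × 4 (time point) mixed ANOVA to examine if there are significant differences in changes in ABC scores between the groups". Only if that interaction is significant are there two post-hoc tests. One is a paired t-test that "will be used to compare ABC scale in the intervention group at 0 and 25 weeks and independent samples" t-test between the groups at week 25. No change is tested or estimated for the control arm, and no between-arm difference in change is named as a follow-up estimate. (The final visit is week 24 in some sections and week 25 in others. That is a separate matter; I write final visit below.)

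**The concern.** When people are admitted because a score fell below a cut, some are admitted on a temporarily low score. If that same score is then used as the starting value, the group mean rises on re-measurement without any treatment. A paired test in one arm cannot separate this rise from a treatment effect. Nor can it remove a response to attention or to taking part, which is what the Sham-control condition section says the control arm is there to absorb.

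The interaction says that the arms changed differently, not which arm moved. The paired result is what a reader will use to say that CBPT raised confidence, and by how much. If the interaction came partly from decline among controls, a non-treatment rise in the CBPT arm could make it look like improvement with CBPT.

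**Working it through.** **The plan's own figure first.** The sample-size paragraph under Participants gives a detectable effect f = 0.152 for the interaction (30 per arm, four time points, correlation 0.50, alpha 0.05, power 0.80). With λ = f² × N × m / (1 − ρ) = 0.152² × 60 × 4 / 0.50 = 11.1 on 3 and 174 degrees of freedom, power is 0.798. Power of exactly 0.80 needs f = 0.1524. The figure reproduces, and it concerns a between-arm contrast in change.

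**Inputs for the within-arm gain**
- Cut: ABC below 80 (Participants).
- Share of the population below the cut: 65%. Background reports 65% below an intervention threshold but does not say that this threshold is 80, so this is an assumption; range tried 50% to 80%.
- Correlation ρ between the qualifying and the later score, before selection: 0.91 is the reliability quoted under Balance confidence, from older adults with fear of falling; 0.70 and 0.50 are assumed.
- Normal scores, no true change, and the qualifying score reused as week 0. All three are assumptions.

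**Formula.** The cut is at c = Φ⁻¹(0.65) = 0.385 SD. The selected mean lies φ(c)/0.65 = 0.570 SD below the population mean, and the selected variance is 1 − 0.385 × 0.570 − 0.570² = 0.456. The expected rise on re-measurement is 0.570 × (1 − ρ).

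| ρ | Spurious rise (population SD) | ABC points if SD is 20 (assumed) | Points over 50–80% selected, SD 15–25 |
|---|---|---|---|
| 0.91 | 0.570 × 0.09 = 0.05 | 1.0 | 0.5 to 1.8 |
| 0.70 | 0.570 × 0.30 = 0.17 | 3.4 | 1.6 to 6.0 |
| 0.50 | 0.570 × 0.50 = 0.28 | 5.7 | 2.6 to 10.0 |

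Selection lowers the correlation seen in the trial sample to ρ√0.456 / √(0.456ρ² + 1 − ρ²). At ρ = 0.70 this is 0.473/0.856 = 0.55, near the protocol's 0.50. At ρ = 0.50 it is 0.338/0.930 = 0.36, below the protocol's own input, so I treat the last row as an outer bound.

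**What is and is not affected.** Simulation with no treatment effect, 30 per arm and the score reused, at ρ = 0.91 / 0.70 / 0.50:
- mean gain, CBPT 1.02 / 3.45 / 5.69 points and control 1.02 / 3.43 / 5.65, so the difference is essentially zero;
- interaction significant in 4.7% / 5.0% / 5.2% of trials;
- between-group test at the final visit significant in 4.8% / 5.0% / 5.1%;
- significant paired gain in CBPT after a significant interaction in 1.0% / 1.9% / 2.3% of all trials.

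With a fresh week-0 score, the mean gain is 0.00 to 0.04 points in either arm.

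**When the gate opens for a real reason.** Suppose CBPT does not change and controls decline by 0.4 to 0.6 SD (assumed), with the score reused. Among trials with a significant interaction, the CBPT paired test shows a significant gain in about 9% at ρ = 0.91, roughly a quarter to a third at 0.70, and roughly half at 0.50. With a fresh week-0 score it is at most about 7%.

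**The case against.** The strongest reply is that nothing confirmatory is at risk, and this stands. Both arms are chosen by the same rule, so regression to the mean cancels in the randomised comparison. A reader might infer that the entry rule inflates the Hypothesis 1a result or its false-positive rate; the simulated 4.7% to 5.2% shows that it does not.

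A reader might also infer that selection by itself must raise the CBPT gain. The documents do not support that. It requires the qualifying score to be reused, and no section says so. VA recruits mail theirs back before consent, and Study design has survey outcomes completed at the start of the study, which points to a second administration. For community recruits the article is silent, and a condensed article may leave that detail to the full protocol.

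Third, an ungated paired test would show a false gain in about 9%, 23% and 37% of null trials at the three correlations. Those are not error rates of this plan, which runs the test only after a significant interaction. That gate is a real protection when neither arm changes. It is none when the interaction reflects control decline or a true effect, since any spurious rise is then carried in the reported gain.

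Finally, the companion test at the final visit is randomised and unbiased. That too stands, but it compares levels, so the only follow-up statement about change remains the uncontrolled one.

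**Conclusion.** The point holds as a limited one about interpretation. The planned paired t-test cannot measure how much CBPT improves ABC, because the within-arm gain carries whatever non-treatment change occurs. Regression to the mean is one possible part of it: about 0.05 population SD at a correlation of 0.91, about 0.17 SD at 0.70, and close to zero if week 0 is measured afresh. These sizes rest on normal scores, 65% of the population lying below 80, and reuse of the qualifying score. The first two are assumptions, and the third is not stated in the article. The entry criterion is sound for the question asked, and the primary test is unaffected. This is a cheap improvement, not a flaw in the trial's main inference.

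**What to change.** In the Analysis plan, replace the post-hoc paired t-test as the measure of improvement with the CBPT-minus-control difference in ABC change from week 0 to the final visit, with a confidence interval. Show each arm's mean change as description only. The between-group comparison of levels can stay.

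State that the week-0 ABC is taken at the enrolment visit, before the allocation envelope is opened, and is a separate administration from the qualifying score wherever the two would otherwise coincide.

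Cost: a sentence or two of text and, for some community recruits, one extra 16-item questionnaire. The reported gain may look smaller than the raw within-arm change, and a few participants may have a week-0 ABC of 80 or above. Precision need not suffer: with equal variances σ² and the protocol's correlation of 0.50, a change score has variance 2σ²(1 − 0.50) = σ², the same as a single final score.

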**Methods/design:**

This randomized control trial will recruit 60 people who use LLP with low balance confidence. Participants will be randomized to the CBPT intervention condition or control condition.

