## Methods/design

### Study design

Sixty people who use LLP with low balance confidence will be randomized to the CBPT intervention condition or control condition (Fig. 1). Participants will be assigned to one of two randomization plans based on etymology of amputation: vascular causes (e.g., diabetes, peripheral vascular disease) or non-vascular causes (e.g., trauma, osteomylistis). For each plan, a block randomization will be used with a block size of 4 to ensure balance among the exercise groups throughout the study. The randomization plan will be developed by a researcher uninvolved with the project using www.randomization.com and sealed envelopes will be used to conceal the randomization schedule until enrolled participants are assigned to a group. For scheduling purposes, to ensure that the necessary clinicians are on site at the time that group assignment is revealed to the participant (at visit occurring ~ 1 week following enrollment), envelopes will be opened after the participant leaves the university after completing the enrollment visit.

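### The protocol does not settle whether 60 is the number randomised or the number expected to complete; if 60 are randomised, the assumed 15% drop-out is not covered and the stated detectable effects are optimistic

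*Protocol article*

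**What the plan says.** The protocol article gives the trial's size in three places.

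- **Abstract, Methods/design:** "This randomized control trial will recruit 60 people who use LLP with low balance confidence". The next sentence has participants randomised, without repeating a number.
- **Study design:** "Sixty people who use LLP with low balance confidence will be randomized to the CBPT intervention condition or control condition".
- **Participants:** "It is expected that 70 participants will be recruited in order to obtain a total of 60 eligible participants". The 60 are divided equally between the arms, and the allowance for loss is worded as "assuming a 15% drop-out rate".

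The Participants section then builds its power statement on the 60. It runs a sensitivity analysis "specifying a power of 0.80, an alpha of 0.05, and an average correlation of observations of 0.50" and concludes that "with 30 participants in each group we will be able to detect a small to medium effect (f = 0.152") for Hypothesis 1a. It adds "we will have power to detect a medium effect size (d = 0.46) for Hypothesis 1b" and a correlation of 0.42 or more for Hypothesis 3.

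Study design describes drop-out as loss between baseline and the final follow-up, and plans contact with participants and data retrieval to limit it. The Key informant interview section also provides for an interview at drop-out. In this article, then, drop-out means leaving after enrolment.

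**The concern.** The abstract and the Participants section attach different numbers, 60 and 70, to recruitment. The Participants section also explains the step from 70 to 60 by a drop-out rate, yet calls the 60 *eligible*. That merges two losses: people found ineligible before allocation, and people who leave after it. Only the second reduces the number analysed among those randomised.

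The number randomised determines when enrolment can close and what power the trial has. If the figure in Study design is followed, the 30 per group behind every detectable effect would be available only if nobody is lost, whereas the article assumes 15%. The article gives recruitment as running to an anticipated end of December 2020, so at publication the choice of target still mattered.

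**Working it through.** **Inputs.** 60 randomised (Study design); 70 recruited to obtain 60, 30 per arm, 15% drop-out, power 0.80, alpha 0.05, correlation 0.50, f = 0.152, d = 0.46, r = 0.42 (Participants); two groups and four time points, tested by the group-by-time interaction (Analysis plan); Hypothesis 3 in the intervention arm only (Aim 3). Sphericity is assumed. The sidedness of the tests behind d and r is not stated.

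**1. Reproduce the stated f.** For the within-between interaction, the noncentrality is λ = f² × N × m / (1 − ρ), with df1 = (k − 1)(m − 1) and df2 = (N − k)(m − 1). With k = 2, m = 4, ρ = 0.50 and N = 60:

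- df1 = 3, df2 = 58 × 3 = 174.
- λ at f = 0.152 is 0.023104 × 60 × 4 / 0.5 = 11.09, giving power 0.798.
- The f for 80% power is 0.1524.

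The stated 0.152 is reproduced, and it requires 60 analysed.

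**2. Reproduce the step from 70 to 60.** 60 / 0.85 = 70.6, and 70 × 0.85 = 59.5. The 70 is what inflating 60 completers for 15% attrition gives, to rounding. With 70 randomised, detectable f is about 0.153 and power at f = 0.152 is about 0.79, so the power statement holds.

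**3. Randomise 60 instead.** 60 × 0.85 = 51. With N = 51:

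- df2 = 49 × 3 = 147.
- λ at f = 0.152 is 0.023104 × 51 × 4 / 0.5 = 9.43, giving power 0.72.
- The f for 80% power is 0.166.

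**4. Within-arm hypotheses.** These use the noncentral t: for d, noncentrality d√n with n − 1 df; for r, noncentrality √(n r² / (1 − r²)) with n − 2 df. At n = 30, the stated values are matched only by one-sided tests, so the effect of drop-out is assessed on that basis. 51 completers over two arms means 25 to 26 in the CBPT arm.

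| One-sided, 80% power | Stated | n = 30 | n = 25 to 26 | Power at stated value, n = 25 to 26 |
|---|---|---|---|---|
| d, Hypothesis 1b | 0.46 | 0.465 | 0.50 to 0.51 | 0.72 to 0.74 |
| r, Hypothesis 3 | 0.42 | 0.422 | 0.45 to 0.46 | 0.73 to 0.74 |

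Under the exact bivariate-normal distribution, r is 0.437 at n = 30 and 0.47 to 0.48 at n = 25 to 26.

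**5. Test each reading against the text.**

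- *70 randomised, about 60 completing:* the power paragraph holds, but Study design and the abstract are wrong.
- *70 consented, 60 randomised after screening:* Study design agrees with the Participants section, but the abstract's 60 recruited does not. The 15% becomes screening loss, and nothing covers the drop-out that Study design expects after baseline.
- *60 recruited and randomised:* the 70 has no role, and again no allowance remains.

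No reading makes every statement hold.

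**The case against.** The strongest reply is that an allowance for drop-out is already planned. The 70 matches 60 / 0.85, the power figures use the 60 that remain, and the abstract and Study design may simply be quoting the evaluable target as a headline. That is plausible, and perhaps the likeliest intention. It still leaves Study design wrong, because it attaches the 60 to randomisation.

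A second reply is that screening follows consent (Participants), so 70 could be consented and 60 randomised. The word *eligible* supports this, but it leaves post-baseline loss uncovered.

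A third reply stands in part. Fifty-one is a complete-case count. The Analysis plan says that missing data will be accounted for in the Hypothesis 1a analysis, and Study design promises efforts to obtain baseline and final self-report data from those who leave. Power for Hypothesis 1a therefore lies between 0.72 and 0.80, and the upper end needs essentially no loss of information. For Hypothesis 1b the outcome is measured at 8 weeks, so applying the whole 15% there is also an upper bound, since the timing of drop-out is not given.

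Four stronger readings are tempting but not supported:

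- **Two-sided comparison.** A reader might set two-sided values at n = 26 (d = 0.57, r = 0.52 by the exact method) against the stated 0.46 and 0.42 and blame drop-out for the gap. But two-sided values at n = 30, with no drop-out, are already 0.529 for d and 0.468 to 0.485 for r. Much of that gap comes from the change of sidedness.
- **A commitment to stop at 60.** The article sets no enrolment stopping rule, so the loss of power is conditional on 60 being the number randomised.
- **Two statements that 60 are randomised.** Only Study design says so; the abstract says that 60 are recruited.
- **59.5 against 60.** This is rounding and has no practical effect.

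**Conclusion.** The inconsistency is real and needs correction. Its effect on power is moderate and conditional. If 60 is the number randomised and 15% drop out, the loss for Hypothesis 1a is at most about 8 percentage points, and a detectable f of 0.166 would still fit the article's description of a small to medium effect. The within-arm figures worsen by about 0.04 to 0.05 for d and 0.03 to 0.04 for r, like for like. If 70 are randomised, the stated figures stand to rounding and only the wording elsewhere is wrong.

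Confidence is high for the conflict between the sections. The size of the power loss rests on the article's own 15%, on near-equal loss in the two arms, on sphericity, and, at the lower end, on no information being recovered from those who leave.

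**What to change.** State one number randomised in the abstract, Study design and Participants. There are two consistent choices:

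1. Make the 70 already planned the number randomised, say that about 60 are expected to complete, and correct the abstract and Study design. The stated detectable effects can then stay.
2. Keep 60 randomised, say that about 51 are expected to complete, and restate the detectable effects: f up to 0.166, d about 0.50 to 0.51 and r about 0.45 to 0.46, naming the last two as one-sided if that is the basis intended.

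In either case, give the expected loss before randomisation (ineligible at screening) separately from drop-out after it, and replace *eligible* with a term that says which stage is meant.

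The cost is a few sentences and, under the second choice, recalculated figures. Neither choice asks for enrolment beyond the 70 that the Participants section already plans.
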